Radiographic appearance (anteroposterior and lateral X-ray at one year): heterotopic ossification will be classified according the classification scheme of Broberg and Morrey as a bone exostosis or as a soft tissue ossification of a ligament, capsule or muscle ("myositis ossificans") [23]; degenerative changes will be classified as grade zero (no change), grade 1 (slight narrowing of the joint space with small osteophytes), grade 2 (moderate narrowing of the joint space, osteophytes and subchondral sclerosis), and grade 3 (severe narrowing of the joint space, large osteophytes, subchondral sclerosis and cystic deformation).

The incremental cost-effectiveness ratio of functional versus plaster treatment will be expressed in a cost-utility ratio, i.e., in terms of cost per QALY. The economic evaluation will be performed from a societal perspective, and will include both health care costs and costs of production losses. Health care costs will include costs of general practice care, medical specialist care, physical therapy, hospitalization, medication, and other costs directly associated with diagnosis, treatment and rehabilitation. Patients will be asked to administer a custom-made questionnaire to register their health care needs and production loss.

In addition to the outcome variables mentioned above, the following data will be collected:

a) Intrinsic variables (baseline data): age, gender, American Society of Anesthesiologists' ASA classification, tobacco consumption, alcohol consumption, comorbidity, social status/household composition, dominant side, and medication use.

b) Injury related variables: affected side, mechanism of injury, and assessment of varus, valgus and posterolateral rotatory instability.

c) Intervention-related variables: reduction delay (i.e., time between dislocation and reduction), time between injury and start of physical therapy, days of sling use, and number of physical therapy sessions

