### Study procedures [Table 1]

**Table 1 T1:** Schedule of events

	Screening	Enrollment	Baseline	1 week	3 weeks	6 weeks	3 months	6 months	12 months
				(3-10 d)	(11-28 d)	(4-8 we)	(11-15 we)	(5-7 mo)	(12-14 mo)
**Screening**	X								

**X-ray**	X		X (<24 h post-reduction)	X					X

**Informed Consent**		X							

**Randomization**		X							

**Baseline data**			X						

**Clinical follow-up**				X	X	X	X	X	X

**Revisision surgery**				X	X	X	X	X	X

**Complications**				X	X	X	X	X	X

**Pain (VAS)**				X	X	X	X	X	X

***Quick-*DASH**						X	X	X	X

**MEPI**						X	X	X	X

**Oxford Elbow Score**						X	X	X	X

**SF-36**						X	X	X	X

**EQ-5D**						X	X	X	X

**Health care consumption**						X	X	X	X

**ROM**						X	X	X	X

**Early withdrawal**				*	*	*	*	*	*

*, only if applicable

Clinical assessments will occur at the time of admission (baseline), one week (3-10-day window), three weeks (11-28-day window), six weeks (4-8-week window), three months (11-15-week window), six months (5-7-month window), and 12 months (12-14-month window) after start of treatment.

At each FU visit, the research coordinator or research assistant will ascertain patient status (i.e., secondary interventions, adverse events/complications, deaths) and will verify information within medical records.

At each FU visit, the patients will be asked to indicate the pain level on a VAS.

At each visit from six weeks onwards, the ROM of the elbow will be measured using a goniometer by a doctor blinded for the treatment of the dislocation. This will be used to calculate the MEPI index. In addition, patients will be asked to complete the questionnaires relating to disability (*Quick-*DASH score including optional modules, Oxford Elbow Score), health-related quality of life (SF-36, EQ-5D), and healthcare consumption.

Plain X-rays of the elbow will be made at the time of presentation in the hospital (baseline), post-reduction, and at the follow-up visit after one week and one year. The X-ray at 12 months will be taken in order to determine the amount and location of heterotopic ossification and the grade of degenerative joint changes. This is common practice in this type of patient. At the last visit, the surgeon will document any surgery that may be planned for the patient.

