### Statistical analysis

Data will be analyzed using the PASW Statistics version 18.0.1 or higher (SPSS, Chicago, Illinois, USA). Normality of continuous data will be tested with the Shapiro-Wilk and Kolmogorov-Smirnov test and by inspecting the frequency distributions (histograms). The homogeneity of variances will be tested using the Levene's test.

The analysis will be performed on an intention to treat basis. Patients with protocol violations will be followed up, and data will be recorded. Data will be analyzed with and without inclusion of patients with protocol violation.

Descriptive analysis will be performed to report baseline characteristics (intrinsic variables and injury-related variables) in both treatment groups. For continuous data (e.g., age, Quick-DASH score at baseline) mean ± SD (parametric data) or medians and percentiles (non-parametric data) will be calculated. For categorical data (e.g., gender, ASA grade, alcohol and tobacco consumption, dominant and affected side) frequencies will be calculated.

The mean difference between the mean *Quick-*DASH scores of the functional group and the plaster group will be tested. Univariate analysis will be performed to test the difference in the primary and secondary outcome measures between the functional and the plaster groups. Continuous data will be tested using a Student's T-test (parametric data) or a Mann Whitney *U*-test (non-parametric data). Chi-square analysis will be used for statistical testing of categorical data. A p-value <0.05 will be taken as the threshold of statistical significance.

A multivariable linear regression analysis will be performed to model the relationship between different covariates and the *Quick-*DASH score. Intrinsic and injury-related variables that display a p-value <0.5 in the univariate analyses will be added as a covariate.

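### Cost per QALY is promised, but EQ-5D starts at six weeks, so no utility is observed while the arms differ by protocol

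*Protocol article*

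**What the plan says.** All places are in the protocol article.

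- **Outcome measures** lists cost and cost-effectiveness among the secondary outcomes. The incremental ratio is to be "expressed in a cost-utility ratio, i.e., in terms of cost per QALY". On the cost side, "The economic evaluation will be performed from a societal perspective, and will include both health care costs and costs of production losses".
- **Study procedures** ties the questionnaires to the later visits. The paragraph opens "At each visit from six weeks onwards, the ROM of the elbow will be measured" and then adds the questionnaires on disability, "health-related quality of life (SF-36, EQ-5D), and healthcare consumption". Table 1 agrees: EQ-5D and SF-36 are marked at six weeks and at three, six and 12 months only. The first of these visits is "six weeks (4-8-week window").
- **Baseline data**, introduced as "Intrinsic variables (baseline data): age, gender" and so on, contain no EQ-5D, SF-36 or other utility measure.
- **Intervention** gives the plaster arm three weeks of immobilisation, while physical therapy in the functional arm begins after two days.
- **Statistical analysis** applies one rule to continuous primary and secondary outcomes: "T-test (parametric data) or a Mann Whitney *U*-test (non-parametric data"). It makes no exception for costs.

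**The concern.** A QALY is the area under the utility curve over the horizon, and here follow-up runs for 12 months from the start of treatment. The curve has no observed point before about week six. That stretch contains the whole period in which the two arms receive different care by protocol: once the plaster is off, that arm follows the same physical therapy protocol. If the treatments differ in quality of life, this is a plausible time for it, and the trial will not have measured it.

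The gap cannot be closed in the analysis. An analysis plan can choose how to impute, but it cannot supply values that were not collected. SF-36 follows the same schedule and offers no substitute. Pain VAS is collected at one and three weeks but is not a utility.

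At stake is the size of the incremental QALY, and so of the cost-effectiveness ratio. The cost comparison raises a smaller matter: the stated rule may lead to a test of something other than the mean cost difference that enters the ratio.

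**Working it through.** The protocol gives no figure for the economic endpoint, so there is none to reproduce. Its sample size of 41 per group concerns Quick-DASH and plays no part here.

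**1. Share of the year without observed utility.** Inputs: first EQ-5D at six weeks, window four to eight weeks (Study procedures); horizon 52 weeks.

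- Nominal: 6/52 = 11.5%
- Window limits: 4/52 = 7.7% and 8/52 = 15.4%
- Plaster period alone: 3/52 = 5.8%

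Even the earliest permitted EQ-5D, at four weeks, comes after scheduled plaster removal at three weeks.

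**2. QALYs that would go unobserved.** The documents give no utilities, so the gap between arms is assumed.

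- Gap 0.1 for three weeks: 0.1 × 3/52 = 0.0058
- Gap 0.3 for three weeks: 0.3 × 3/52 = 0.0173

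A constant gap over the remaining 46 weeks that yields the same QALYs is 0.1 × 3/46 = 0.0065 to 0.3 × 3/46 = 0.0196.

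**3. How much depends on the choice of assumption.** Assumed utility differences (functional minus plaster) are 0 at baseline, *d* at weeks 1 and 3, 0.02 at week 6, 0.01 at week 13, and 0 at weeks 26 and 52. The trapezoid rule in utility-weeks gives:

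- Weeks 0 to 6, *d* = 0.10: 0.05 × 1 + 0.10 × 2 + 0.06 × 3 = 0.43
- Weeks 0 to 6, *d* = 0.20: 0.10 × 1 + 0.20 × 2 + 0.11 × 3 = 0.83
- Weeks 6 to 52, either case: 0.015 × 7 + 0.005 × 13 = 0.17
- Week-six difference carried back: 0.02 × 6 = 0.12, so 0.12 + 0.17 = 0.29

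Dividing by 52, and taking an assumed cost difference of 500:

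| | QALY, *d* = 0.10 | QALY, *d* = 0.20 | Cost per QALY |
|---|---|---|---|
| Full curve | 0.60/52 = 0.0115 | 1.00/52 = 0.0192 | 43,333 / 26,000 |
| Week 6 onward only | 0.17/52 = 0.0033 (28%) | 0.0033 (17%) | 152,941 |
| Week 6 carried back | 0.29/52 = 0.0056 (48%) | 0.0056 (29%) | 89,655 |

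The last two rows are the same for both values of *d*: the data as scheduled cannot tell the two cases apart.

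**4. The cost test.** Simulation on assumed lognormal costs, 40 per arm, 20,000 runs:

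- Equal means (3000), log-SDs 0.6 and 1.2: Mann-Whitney rejects in 68% of runs, Welch in 10%.
- Equal medians, means 3000 and 5148: Mann-Whitney rejects in 6%, Welch in 29%.
- Identical distributions (mean 3000, log-SD 1): both stay near nominal, at 4.7% and 4.0%.

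Shapiro-Wilk rejected normality in at least 93% of the samples checked. The rank test and the mean difference part company when the spreads differ between arms.

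**The case against.** The strongest reply is that the article states no QALY formula and no handling of the early weeks, and that such detail commonly sits in a fuller document. That stands for the method of calculation. It does not stand for the visit schedule, which Table 1 and the text fix consistently. The mention of a baseline Quick-DASH in Statistical analysis does not show that a baseline EQ-5D exists.

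The early contrast may also be modest: both arms are advised to use a sling, and the early exercises in the functional arm are restricted. That is fair, and is why the 0.1 to 0.3 gap is only an illustration.

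A reader might infer four stronger things that the documents do not support:

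- *That cost per QALY cannot be estimated.* It can, from week six onward or with an imputed early value. What is not available is a full 12-month estimate from observed utilities.
- *That the plan sets the early difference to zero.* It states no such rule. Carrying the week-six value back assumes that the week-six difference held earlier. Zero follows only if the early weeks are dropped or the arms have converged by week six.
- *That the conclusion could change sign.* No calculation here shows this, and the documents give no utilities from which to show it.
- *That the rank test undermines the ratio.* Mean costs, and so the ratio, can be computed whatever test is applied. That costs are skewed is likely but assumed, and the unequal spreads in the simulation were chosen to show the divergence.

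**Conclusion.** The point holds as a gap in data collection. Observed utilities miss about 11.5% of the year (7.7% to 15.4% over the visit window), including the entire plaster period, so a 12-month QALY difference must either omit that time or rest on an untestable assumption. These facts come directly from the schedule. The QALY amounts, the ratios and the cost simulation all rest on assumed values and show only that the choice of assumption can matter.

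The consequence is confined to a secondary outcome; the Quick-DASH comparison and its sample size are unaffected. The change is still worth making, because early values not collected cannot be recovered later. The cost-test point is subsidiary: read literally, the rule sends non-normal costs to a test that does not address the mean difference, but it neither prevents nor alters the ratio.

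**What to change.** 1. In Table 1 and the accompanying text, add EQ-5D at the existing one-week and three-week visits, and at baseline after consent where feasible. Baseline needs that qualification because patients are informed only after reduction and are randomised within a week.
2. State that QALYs are the area under the utility curve from the start of treatment, using actual assessment dates. The three-week window (11 to 28 days) runs past scheduled plaster removal, so nominal dates would misplace some values.
3. For patients already past week three, state the imputation assumption for the early period and vary it in a sensitivity analysis.
4. For costs, report the difference in mean cost with a bootstrap confidence interval instead of relying on the general t-test or Mann-Whitney rule.

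The cost is a short questionnaire at contacts that already take place, a slight patient burden, and a minor amendment across 25 centres whose local approvals are already in place. Recruitment began in August 2009 at an expected eight patients a month, about 100/8 = 12.5 months in all, so the benefit shrinks the later the amendment comes. Items 2 to 4 need no new data.

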Three observational studies comparing different periods of plaster immobilization after reduction showed a larger ROM after shorter immobilization, but this finding was statistically significant in only one study [9-11]. Moreover, these studies may be confounded by the severity of the injury, as worse cases were probably immobilized longer.

An important question following reduction of simple elbow dislocations is whether or not the elbow is stable. Signs of instability are redislocation, a positive pivot shift test, positive valgus and varus stress testing, and radiographic incongruence. In the studies described above, stability testing was either not performed, or the tests differed between the studies. In these eight studies, only one recurrent dislocation after plaster treatment was mentioned [7] (i.e., one recurrence in 342 patients (0.3%)), and signs of gross instability were not mentioned. Therefore, we conclude that the majority of the patients included in these studies had simple dislocations, which remained stable after reduction. For this type of dislocation, literature suggests that plaster immobilization for more than two weeks following reduction may lead to limited ROM [12,13]. Therefore some authors state that early functional treatment should be the treatment of choice. Functional treatment is defined as early active movements within the limits of pain with or without the use of a sling or a hinged brace [6-8].

A recent electronic survey of 90 trauma surgeons in the Netherlands revealed that 60% of the patients with a simple elbow dislocation were generally treated with plaster immobilization for three weeks or longer [14].

The primary objective of this study is to compare the *Quick-*DASH (Disabilities of the Arm, Shoulder, and Hand) questionnaire scores after functional treatment versus plaster immobilization in adult patients who sustained a simple elbow dislocation. Secondary aims are to examine the effect of functional treatment versus plaster immobilization on functional outcome (Mayo Elbow Performance Index (MEPI) and Oxford elbow score), the level of pain (Visual Analog Scale (VAS)), ROM, the rate of secondary interventions and complications, health-related quality of life (Short Form-36 (SF-36) and EuroQol-5D (EQ-5D)), costs, and cost-effectiveness in these patients.

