### Outcome measures

The primary outcome measure is the *Quick-*DASH (Disabilities of the Arm, Shoulder and Hand) score, which reflects both function and pain [15]. The DASH Outcome Measure is a validated 30-item, self-reported questionnaire designed to help describe the disability experienced by people with upper-limb disorders and also to monitor changes in symptoms and function over time [15,16].

The *Quick-*DASH is a shortened version of the DASH Outcome Measure. Instead of 30 items, the Quick-DASH uses 11 items (scored 1-5) to measure physical function and symptoms in people with any or multiple musculoskeletal disorders of the upper limb. The right and left elbow will be assessed separately. At least 10 of the 11 items must be completed for a score to be calculated. The scores will be transformed to a 0-100 scale for easy comparison. A higher score indicates greater disability.

Like the DASH, the *Quick-*DASH contains 2 optional modules to measure symptoms and function in athletes, performing artists and other workers whose jobs require a high degree of physical performance. These optional models are scored separately; each contains four items, scored 1-5. All items must be completed for a score to be calculated.

The secondary outcome measures are:

• Functional outcome (Mayo Elbow Performance Index and Oxford Elbow Score)

• Pain level at both sides (VAS)

• Range of Motion of the elbow joint at both sides

• Rate of secondary interventions

• Rate of complications (secondary dislocation, instability, relaxation)

• Health-related quality of life: SF-36 and EQ-5D

• Radiographic appearance of elbow joint (degenerative changes and heterotopic ossifications)

• Cost

• Cost-effectiveness

The MEPI index is one of the most commonly used physician-based elbow rating systems. This index consists of five parts: pain (with a maximum score of 45 points), ulnohumeral motion (20 points), stability (ten points), the ability to perform five functional tasks (5 × 5 points) and the patient response. If the total score is between 90 and 100 points, it is considered excellent; between 75 and 89 points, good; between 60 and 74 points, fair; and less than 60 points, poor [17].

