The Oxford elbow score is a 12-item questionnaire. It is comprised of three one-dimensional domains: elbow function, pain and social-psychological, with each domain comprising 4 items with good measurement properties [18]. This is a validated questionnaire in the UK and was translated to Dutch by the proper translation procedure, which uses the technique of translation and back-translation [19]. Permission for translation and the use of the OES for this study was obtained from Oxford and Isis Outcomes, part of Isis Innovation Limited (website: http://www.isis-innovation.com/)

Pain level will be determined using a 10-point Visual Analog Scale (VAS), in which zero implies no pain and ten implies the worst possible pain.

ROM will be measured on both sides using a goniometer.

Secondary interventions within one year of initial treatment to relieve pain or improve function will be recorded. This includes secondary revision of collateral ligaments and external fixator placement.

Complications within one year of initial treatment will be recorded. These include redislocation, pressure necrosis (plaster group only), post-traumatic dystrophy, and neurologic deficit.

The Short-Form 36 (SF-36) is a validated multi-purpose, short-form health survey with 36 questions that represent eight health domains that are combined into a physical and a mental component scale [20]. The Physical Component Scale (PCS) combines the health domains of physical functioning (PF; ten items), role limitations due to physical health (RP; four items), bodily pain (BP; two items), and general health perceptions (GH; five items). The Mental Component Scale (MCS) combines the health domains of vitality, energy, or fatigue (VT; four items), social functioning (SF; two items), role limitations due to emotional problems (RE; three items), and general mental health (MH; five items). Scores ranging from zero to 100 points are derived for each domain, with lower scores indicating poorer function. These scores will be converted to a norm-based score and compared with the norms for the general population of the United States (1998), in which each scale was scored to have the same average (50 points) and the same standard deviation (ten points).

The EuroQol-5D is a validated questionnaire for health-related quality of life [21,22].

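### The comparison of follow-up instability makes no use of the baseline instability examination, so it cannot tell new instability from laxity left by the injury

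*Protocol article*

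**What the plan says.** Among the secondary outcomes, the Outcome measures section lists "Rate of complications (secondary dislocation, instability, relaxation", so instability is handled as a rate. Later in that section, complications recorded within a year of treatment are illustrated by a second list: "These include redislocation, pressure necrosis (plaster group only), post-traumatic dystrophy, and neurologic deficit". Instability is not in it, and no definition of the instability outcome is given.

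The same section collects, as baseline-type data, "Injury related variables: affected side, mechanism of injury, and assessment of varus, valgus and posterolateral rotatory instability". The Background describes the same clinical property: "Signs of instability are redislocation, a positive pivot shift test, positive valgus and varus stress testing, and radiographic incongruence".

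Statistical analysis gives the baseline examination two uses. It is reported by arm: "Descriptive analysis will be performed to report baseline characteristics (intrinsic variables and injury-related variables) in both treatment groups". As an injury-related variable, it may also enter the multivariable linear regression for Quick-DASH. For the outcomes the plan is: "Univariate analysis will be performed to test the difference in the primary and secondary outcome measures between the functional and the plaster groups", and "Chi-square analysis will be used for statistical testing of categorical data". No adjusted or stratified analysis is stated for instability.

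**The concern.** The Abstract's rationale is that early motion should prevent stiffness without adding joint instability. That is a statement about instability arising under treatment. A crude proportion unstable at follow-up can mix two kinds of elbow: those that were stable after reduction and became unstable, and those that were lax after reduction and stayed lax.

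Lax elbows can enter the trial. The exclusion criteria remove recurrent dislocations and patients having collateral ligament repair, but not elbows that test lax after closed reduction. Recruitment and consent describes variable block randomisation and mentions no stratification by laxity.

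Two things are at stake. A difference in new instability can be diluted by persisting laxity common to both arms. With about 50 patients per arm, a chance difference in initial laxity also carries through to the crude comparison. The examination that would address both is collected but is not used for this outcome.

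**Working it through.** **The plan's own figures.** The article states no instability rate and no power for this outcome. Its only design figure is 41 evaluable patients per arm, or 50 with dropout, for Quick-DASH. With means 12.5 and 5, SDs 15 and 7.5 (root mean square 11.86), a two-sided 5% t-test has power 0.798 at 40 per arm and 0.808 at 41, so 41 reproduces. The point does not depend on this; the arm sizes are only borrowed below. **Every instability rate below is an assumption.**

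**1. Precision from the baseline finding (50 per arm).** Let *q* be the share unstable at baseline, and *pu* and *ps* the follow-up instability risks in those unstable and stable at baseline.

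- Overall risk: m = q·pu + (1 − q)·ps
- Variance explained: R² = q(1 − q)(pu − ps)² / [m(1 − m)]
- Crude SE of the risk difference: √[2m(1 − m)/50]
- SE using the baseline finding: crude SE × √(1 − R²)

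First row: m = 0.2×0.40 + 0.8×0.05 = 0.12; R² = 0.16×0.1225/0.1056 = 0.186; crude SE = √(2×0.1056/50) = 6.5 points; √(1 − 0.186) = 0.902.

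| q | pu | ps | m | R² | Crude SE (points) | SE with baseline (points) | Reduction |
|---|---|---|---|---|---|---|---|
| 0.20 | 0.40 | 0.05 | 0.12 | 18.6% | 6.5 | 5.9 | 9.8% |
| 0.20 | 0.20 | 0.05 | 0.08 | 4.9% | 5.4 | 5.3 | 2.5% |
| 0.30 | 0.30 | 0.10 | 0.16 | 6.2% | 7.3 | 7.1 | 3.2% |
| 0.05 | 0.20 | 0.02 | 0.029 | 5.5% | 3.4 | 3.3 | 2.8% |

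The last row is a rare-event case, with about 3 events expected in 100 patients (100 × 0.029).

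**2. Chance imbalance.** The SD of the between-arm difference in baseline laxity is √[2q(1 − q)/50]. At q = 0.20 this is 8.0 points. Multiplied by pu − ps = 0.35, it moves the crude difference by 2.8 points per SD, to be set against the crude SE of 6.5. At 1.96 SD the figures are 5.5 and 12.7. This variation is already part of the crude SE (2.8²/6.5² = 0.186 = R²). It is not an extra error; it is the part that stratification can remove.

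**3. Dilution (41 per arm).** Assume new instability of 15% versus 5% in elbows stable at baseline, 20% lax at baseline in both arms, and laxity that persists and is counted.

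- Crude rates: 0.20 + 0.80×0.15 = 32% and 0.20 + 0.80×0.05 = 24%.
- The risk difference falls from 10 to 8 points and the risk ratio from 3.0 to 1.33. If only half the laxity persists, the rates are 23.5% and 14.5%, ratio 1.62.
- Power by normal approximation is 0.12 for the crude comparison, against 0.27 for new instability among the patients stable at baseline (41×0.8 ≈ 33 per arm). Both are low.

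A Mantel-Haenszel risk difference alone does not undo this dilution. In this example the stratum differences are 0 and 10 points with weights 0.2 and 0.8, giving 8 again. Stratification deals with imbalance and precision; separate reporting of new instability deals with dilution.

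**4. Validity.** With equal risks in both arms, the simulated type I error of the unadjusted test at 41 per arm was 0.049, 0.051 and 0.057 at 10%, 20% and 40% baseline laxity. The crude test therefore stays close to its nominal level.

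**The case against.** The strongest reply is that the planned test is sound. Allocation is random, an unadjusted chi-square test is a usual choice for a secondary binary outcome, and the baseline examination will be reported by arm, so a marked imbalance would be visible. The rates used above are invented. The nearest figures in the article point to rare events: the Background reports one recurrence in 342 patients (0.3%) and no mention of gross instability. With few events, stratification gains little and can become sparse. How a complication qualifies as new may also be set out in a full protocol or analysis plan that is not shown.

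Most of this stands, and it limits the point to one of precision and interpretation. It does not remove the point. Reporting initial laxity by arm does not show which elbows were newly unstable. The article also states the comparison it will use, so this is a stated choice that can be improved rather than a missing detail.

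A reader might infer more: that the plan counts injury laxity as a treatment complication, or that the comparison is biased. The article supports neither. No section says that instability present at baseline is counted. The outcome is undefined and is absent from the second list of complications, which is not worded as exhaustive. Randomisation balances initial laxity in expectation.

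**Conclusion.** The point holds as a minor one, for a secondary outcome only; the primary analysis and the sample size are unaffected. Follow-up instability is compared by a crude test that is valid but makes no use of a relevant baseline examination. Nothing stated in the article prevents laxity from the injury being counted along with new instability. Under the assumed rates the baseline finding explains about 5% to 19% of outcome variance and lowers the standard error by about 2.5% to 10%. The upper figure needs a strong link between baseline and follow-up instability. If instability is rare, or stress testing of a painful elbow is noisy, the gain is small. The benefit for interpretation, telling new from persisting instability, does not depend on a large gain in precision, but it too relies on a reasonably reliable baseline examination.

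**What to change.** In Statistical analysis, state that follow-up instability will be compared between arms stratified by the baseline finding (unstable in any direction, yes or no), for example as a Mantel-Haenszel risk difference with 95% confidence interval. State also that new instability among patients stable at baseline will be reported by arm, separately from persisting instability in those unstable at baseline. In Outcome measures, say whether instability belongs to the recorded complications, so that the two lists agree.

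The stratified comparison and the split into new and persisting need only the planned baseline examination and the follow-up instability outcome, so the cost is mainly wording. A follow-up table for each direction should be left out unless that examination is already recorded at follow-up; the schedule of events has no row for it, and adding one would change data collection in a trial already recruiting. The article does not say whether the baseline examination is made before allocation is known. That should be stated when the result is used as a stratifier.
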